#### 4.9 Interim analyses

Not applicable.

### 5 QUALITY CONTROL

The SAP was reviewed by the Trial Statistician (TS) before signature. Particularly the TS has checked the consistency of the described methods and outputs with the actual version of the study protocol. In addition, a sponsor representative has reviewed the SAP before final approval.

Log files of all SAS® programs used in the analysis will be checked for errors, warnings and suspicious notes by the statistical programmer. All findings will be either eliminated or commented upon. The final version of each program will be stored along with its log file in the electronic archive.

All programs will be validated by the program author or an independent statistical programmer depending on the requested validation level selected in the List of TLFs.

The agreement of the program outputs with the SAP, their consistency and plausibility will be checked by the TS. Moreover, the TS will review the outputs regarding completeness, readability and comprehensibility.

The described process is associated with the 'normal' level of program validation. Additional levels of quality control can be specified in the List of TLFs (see Appendix, 1) for individual outputs.

|                           |                 |             |               |
|---------------------------|-----------------|-------------|---------------|
| Statistical Analysis Plan | Version 2.0     |             | Page 18 of 19 |
| Sponsor                   | [name] | Protocol No | FARES         |

## 6 DERIVATIONS AND TRANSFORMATIONS

### 6.1 Formulas for derived variables

| Variable                               | Definition / Derivation                                                                                                                                                                                                                                                                                                                                                                                                                                                                            |
|----------------------------------------|----------------------------------------------------------------------------------------------------------------------------------------------------------------------------------------------------------------------------------------------------------------------------------------------------------------------------------------------------------------------------------------------------------------------------------------------------------------------------------------------------|
| Response (4h)
(Treatment response)  | 
= 'Effective' ('Yes') if no additional hemostatic intervention occurred (such as administration of hemostatic agents including a second dose of IMP, platelet transfusion, or surgical re-exploration) from 60 minutes to 4 hours after initiation of the first dose of IMP.
 
= 'Ineffective' ('No') otherwise.
 
If the dose of IMP is repeated within less than 60 minutes, treatment response to the IMP will be assessed for the 60 minutes after the second IMP dose only.
  |
| Response (24h)
(Treatment response) | 
= 'Effective' ('Yes') if no additional hemostatic intervention occurred (such as administration of hemostatic agents including a second dose of IMP, platelet transfusion, or surgical re-exploration) from 60 minutes to 24 hours after initiation of the first dose of IMP.
 
= 'Ineffective' ('No') otherwise.
 
If the dose of IMP is repeated within less than 60 minutes, treatment response to the IMP will be assessed for the 60 minutes after the second IMP dose only.
 |
| ABP(time frame)                        | = Sum of all Allogenic Blood Products (RBCs, FPs and Platelets) transfused in specified time frame                                                                                                                                                                                                                                                                                                                                                                                                 |
| ABP adj (time frame)        | = Adjusted Sum of Allogenic Blood Products (RBCs and Platelets) transfused in specified time frame, I.e. ABP excluding FPs                                                                                                                                                                                                                                                                                                                                                                         |

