#### Prothrombin Complex Concentrate

PCC offers a potential alternative to FP for treating bleeding cardiac surgery patients requiring coagulation factor replacement. PCCs contain prothrombin and other enzymatic coagulation factors, the anticoagulant proteins C and S and anti-thrombin, and small amounts of heparin; they are routinely defined as 3-factor (that contain factors II, IX, and X) or 4-factor (that contain factors II, VII, IX, and X) formulations (47). PCCs are purified from human pooled plasma, which is fractionated into cryoprecipitate and cryoprecipitate-free plasma fractions through a process of slow thawing, then eluted from cryoprecipitate-free plasma (47). The production of PCCs includes strict viral inactivation using solvents, detergents, pasteurization, nanofiltration, and vapor-heated treatment (5, 47).

PCCs have several potential advantages over FP. Solvent/detergent treatment and filtering to remove viruses substantially reduces the risk of transmission of infectious agents with PCCs. Indeed, a Consensus Conference recommended in 2007 that pathogen reduction technologies should be implemented to improve the safety of transfusion when they became available (48). Unlike FP, PCCs do not require ABO compatibility matching or thawing, and can therefore be prepared and administered more quickly. PCCs are associated with a substantially lower risk of TRALI (due to pooling of the source donor plasma), and also a lower risk of TACO (37), as substantially lower volumes of PCC are required than with FP to achieve dose-equivalence for increasing thrombin generation (for example, in a 70-kg patient, a standard dose of 25 IU/kg PCC would be administered in a volume of 80 mL, whereas a standard dose of 15 mL/kg FP would be administered in a volume of 1000 mL) (46). PCCs contain standardized levels of coagulation factors and thus have a more predictable therapeutic effect than FP, whose coagulation factor concentrations vary depending on the characteristics of the donor (49, 50).

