##### 3.1.1 Efficacy Endpoints

###### *Primary Endpoints:*

1. Treatment response, defined as effective if no additional hemostatic intervention (such as administration of hemostatic agents including a second dose of IMP, platelet transfusion, or surgical re-exploration) from 60 minutes to 4 and 24 hours after initiation of the first dose of IMP (otherwise will be defined as not effective). If the dose of IMP is repeated within less than 60 minutes, treatment response to the IMP will be assessed for the 60 minutes after the second IMP dose only.
2. Amount of allogeneic blood products (for each type of product and cumulatively) administered during the first 24 hours after the start of surgery.
3. Number of patients who do not receive any RBC transfusions or any allogeneic blood transfusions during the first 24 hours after the start of surgery.

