### Revision history

| SAP Version | Version date | Reason(s) for change                                                                                                                                                                                                                                                                                                                                                                                                                                                                                                                               |
|-------------|--------------|----------------------------------------------------------------------------------------------------------------------------------------------------------------------------------------------------------------------------------------------------------------------------------------------------------------------------------------------------------------------------------------------------------------------------------------------------------------------------------------------------------------------------------------------------|
| 1.0         | 2020-04-30   | Not applicable. First version.                                                                                                                                                                                                                                                                                                                                                                                                                                                                                                                     |
| 2.0         | 2020-09-21   | 
Changes required by discussions during Blinded Data Review Meeting:
 
 
• Add exploratory analysis to assess the dependence of treatment response on compliance (section 3.6),
 
• Add exploratory analysis to assess endpoints in different time frames
 
• Add another secondary endpoint applying a conservative response definition.
 
• Clarify that ‘other’ medical history will only be listed and only prespecified conditions will be summarized (section 4.4).
 
 |

|                                  |                        |                    |                     |
|----------------------------------|------------------------|--------------------|---------------------|

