#### 4.6 Efficacy

The primary population for the analysis of the efficacy of the IMPs will be the ITT. The primary efficacy endpoints will also be analyzed for the PP population.

The analysis of efficacy will focus on the following primary endpoints:

P1. Treatment response, defined as effective if no additional hemostatic intervention (such as administration of hemostatic agents including a second dose of IMP, platelet transfusion, or surgical re-exploration) in the time windows

- from 60 minutes to 4 and 24 hours after initiation of the first dose of IMP,
- *from initiation of the first dose of IMP to 4 and 24 hours.*

Otherwise, treatment response will be considered as not effective, see section 6.1. If the dose of IMP is repeated within less than 60 minutes, treatment response to the IMP will be assessed for the time frames after the second IMP dose only.

P2. Amount of allogeneic blood products (for each type of product and cumulatively) administered

- during the first 24 hours after the start of surgery,
- *during the first 24 hours after the end of CPB,*
- *during the first 24 hours after randomization,*
- *during the first 24 hours after the start of first IMP dose.*

P3. Number of patients who do not receive any allogeneic blood product (in total and for each type separately)

- during the first 24 hours after the start of surgery,
- *during the first 24 hours after the end of CPB,*
- *during the first 24 hours after randomization,*
- *during the first 24 hours after the start of first IMP dose.*

In addition the following efficacy endpoints will be explored:

S1. Number of partial or full IMP doses of PCC and FP administered

- during the first 24 hours after the start of surgery.
- *during the first 24 hours after the end of CPB,*
- *during the first 24 hours after randomization,*
- *during the first 24 hours after the start of first IMP dose.*

|                           |                 |             |               |
|---------------------------|-----------------|-------------|---------------|
| Statistical Analysis Plan | Version 2.0     |             | Page 13 of 19 |
| Sponsor                   | [name] | Protocol No | FARES         |

S2. Incidence of major bleeding, using the universal definition of perioperative bleeding (UDPB) in cardiac surgery scores and their individual components

- during the first 24 hours after start of surgery,
- *during the first 24 hours after the end of CPB,*

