Otherwise, treatment response will be considered as not effective. If the dose of IMP is repeated within less than 60 minutes, treatment response to the IMP will be assessed as not effective.

Furthermore, the above mentioned efficacy endpoints will be exploratory analyzed in time frames which start at the time of first IMP dosing instead of the start of the surgery (as specified in section 2.2 of this SAP).

The following analysis methods will be applied to the different endpoints in according to their data type:

The analysis of categorical variables (P1, P3, S2, S4, S5, S6) will present relative frequency tables and estimates of the proportions with 95% confidence intervals separately in the treatment groups. The proportions will be compared between the treatment groups by means of Fisher's exact test.

The analysis of continuous variables (S7, S8) will present descriptive statistics of the sampling distribution and the differences between treatment groups. Also 95% confidence intervals and results of t-test of the treatment group differences will be reported.

The analysis of integer count variables (P2, S1, S3) will present descriptive statistics of the sampling distribution and the differences between treatment groups. Treatment group comparisons for variables (P2, S3) will be performed in the context of a counting regression model for the ABPs and their components (SAS PROC GENMOD with Negative-Binomial distribution). Tests and 95% confidence intervals for the treatment group differences will be derived from this statistical model and reported. The analysis for the sum of the allogenic blood products transfused (P2, S3) will be repeated analogously for the adjusted sum of the allogenic blood products transfused (cf. section 6.1), excluding FP.

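### Treatment response (P1): for a patient redosed within 60 minutes, the protocol and SAP 6.1 decide both the 4 h and the 24 h result on one 60-minute check, while SAP 4.6 uses the full time frames

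*Combined protocol and SAP*

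**What the plan says.** P1 is a yes/no endpoint: no additional hemostatic intervention in the window "from 60 minutes to 4 and 24 hours after initiation of the first dose of IMP" (protocol 3.1.1, repeated in the synopsis). A second IMP dose is itself one of the listed interventions. A special clause covers a second dose given before 60 minutes, and it appears in two forms:

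- Protocol 3.1.1, the synopsis, and both the Response (4h) and Response (24h) rows of SAP 6.1: "treatment response to the IMP will be assessed for the 60 minutes after the second IMP dose only".
- SAP 4.6, under P1: "treatment response to the IMP will be assessed for the time frames after the second IMP dose only".

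SAP 4.6 adds a second P1 window that starts at initiation of the first dose, and its clause covers that window too. SAP 6.1 has no derivation for it.

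SAP 4.6 also defines a separate endpoint, S9, under which: "If the dose of IMP is repeated within less than 60 minutes, treatment response to the IMP will be assessed as not effective". The revision history describes its origin: "Add another secondary endpoint applying a conservative response definition". S9 has no derivation in SAP 6.1, and it is absent from the list assigned to Fisher's exact test: "The analysis of categorical variables (P1, P3, S2, S4, S5, S6) will present relative frequency tables". SAP 2.2 reports no deviations from the protocol's statistical methods.

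**The concern.** Two things look wrong. First, the plan defines one primary endpoint in two ways for the same patients. Second, the rule in the protocol and SAP 6.1 answers a 24-hour question with one hour of data. Patients who needed a repeat dose soonest are then followed for the shortest time, and later interventions do not count against them.

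The pilot exists to choose the Phase 3 primary endpoint, and protocol 1.2 says its results will feed the Phase 3 sample size. A response rate that depends on which SAP section is followed, or that mixes 1-hour and 23-hour outcomes, is a poor basis for either purpose.

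**Working it through.** The documents state no response rate, redose rate or power for P1, so there is no plan figure to reproduce. The check applies each wording as written and then sizes the effect under stated assumptions.

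**1. Length of assessment.** Single-dose patient: 4 − 1 = 3 h and 24 − 1 = 23 h. Patient redosed early, under SAP 6.1: 1 h for both variables, ending less than 60 + 60 = 120 minutes after the first dose.

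**2. The wordings on example patients.** Take dose 2 at 30 minutes, with all times counted from dose 1. The 6.1 window is 30–90 min. Reading the 4.6 time frames as 60 min to 4 h and 24 h after dose 2, the windows are 90–270 min and 90–1470 min.

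| Next event | 6.1, 4h and 24h | 4.6, 4h | 4.6, 24h | S9 |
|---|---|---|---|---|
| None | effective | effective | effective | not effective |
| Platelets at 80 min | not effective | effective | effective | not effective |
| Platelets at 120 min | effective | not effective | not effective | not effective |
| Re-exploration at 10 h (600 min) | effective | effective | not effective | not effective |

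The two P1 wordings disagree in both directions. Against S9, the 6.1 result is never worse.

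**3. The window from initiation.** A second dose at 30 minutes lies inside a window that opens at 0 minutes and is a listed intervention, so the basic definition makes the patient not effective. The re-scoring clause in SAP 4.6 overrides this, and no row in 6.1 settles the matter.

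**4. Size within an arm.** Let r be the share of patients redosed before 60 minutes, q60 the share of those who pass the 60-minute check, and q24 the share who pass the 4.6 window to 24 h. All three are assumed.

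- 6.1 minus S9 = r × q60. At r = 5%: 0.05 × 0.5 = 2.5 points to 0.05 × 0.9 = 4.5 points. At r = 10%: 5 to 9 points, or 2.5 to 4.5 patients of 50.
- 6.1 minus 4.6 = r × (q60 − q24). At r = 10%: 0.10 × (0.9 − 0.5) = +4 points; 0.10 × (0.5 − 0.3) = +2; zero if q60 = q24; 0.10 × (0.4 − 0.5) = −1.

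**5. Size between arms.** Assume 50 per arm (SAP 1.3), a true S9 response of 60% in both arms, q60 of 0.5 to 0.9, and a two-sided 0.05 level (the SAP states none). Exact enumeration of Fisher's test gives:

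| Early redose, PCC vs FP | Artefact in P1 (PCC minus FP) | Rejection probability |
|---|---|---|
| None in either arm | 0 | 3.2% |
| 10% vs 0% | +5 to +9 points | 5.4–11.1% |
| 10% vs 5% | +2.5 to +4.5 points | 3.6–5.0% |
| 5% vs 10% | −2.5 to −4.5 points | 3.6–5.0% |

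The sign follows whichever arm is redosed early more often.

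**The case against.** The defence has real substance.

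- **A governing text exists for the original windows.** SAP 4.6 refers to section 6.1 under P1, SAP section 4 says derived data follow 6.1, and 6.1 matches the protocol. This stands, so to say that two programmers must produce different results would go too far. It does not cover the window from initiation, and it confirms the 60-minute check as the operative rule.
- **The base window already excuses an early redose.** It opens at 60 minutes, so a second dose at 30 minutes was never a failure there, and the clause adds a check. This stands too: the clause does not erase a failure in the protocol's window, and deleting it would not be a full repair. But without the clause, a re-exploration at 10 h would at least count at 24 h.
- **S9 supplies the conservative analysis.** A reader might take S9 as a third, conflicting version of P1. It is a separate endpoint added after blinded review, and P1 minus S9 would show the shift. It lacks a derivation and an assigned test, and it leaves P1 unchanged.

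A reader might also infer that the rule favours PCC. PCC is injected by syringe and is quicker to prepare and give; FP needs matching and thawing, and in a background example for a 70-kg patient, "a standard dose of 15 mL/kg FP would be administered in a volume of 1000 mL". The second dose is not concealed (protocol 3.3.7). That makes a difference between arms plausible. But the documents give no infusion times and no redose rates by arm, and reversed rates reverse the sign.

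Finally, this is an exploratory pilot without a power claim, which limits the harm but not the need for a single definition.

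**Conclusion.** The point holds as a defect in the definition of P1. Followed exactly, SAP 6.1 and the protocol record a patient redosed at 30 minutes and re-explored at 10 hours as effective at 24 hours. SAP 4.6 gives a different answer, and its clause for the window from initiation contradicts that window's own definition.

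Relative to S9, the 6.1 rate is equal or higher with certainty; the 5 to 9 points at 10% early redosing rest on assumed rates. Relative to the SAP 4.6 wording, the sign is open. A bias between arms is possible, but its direction and size cannot be shown from the documents. Nor do they rank P1 above the other two primary endpoints as the Phase 3 candidate.

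A lesser gap belongs to the same definition: it has no rule for death, so a patient who dies in the window without a further intervention counts as effective.

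**What to change.** Before unblinding, write one P1 redose rule with explicit start and end times, running to 4 h and 24 h. Use identical words in the protocol synopsis, protocol 3.1.1, SAP 4.6 and SAP 6.1, and record the change in SAP 2.2.

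- **Preferred:** a second IMP dose at any time from the first dose to 4 h or 24 h counts as not effective (the S9 rule). Keep the protocol's 60-minute re-scoring as a sensitivity analysis.
- **Minimum:** score patients redosed early over the full 4 h and 24 h windows, never on a 60-minute check, and state which dose starts the clock. In the window from initiation, count an early redose as not effective.
- **In either case:** add a 6.1 derivation for the window from initiation, count death within the window as not effective, and report the number of early redoses by arm. If S9 is kept as a separate endpoint, give it a 6.1 derivation and add it to the Fisher's exact test list.

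The cost is wording and some programming. The headline response rate may be slightly lower. Because the clause originates in the protocol, the endpoint text there must be amended as well and submitted to the research ethics board (protocol 10.4); a change to the SAP alone would leave the two documents in conflict.

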| Intraoperative medications                                              |                    | X                                          |                       |                   |
| CPB time                                                                |                    | X                                          |                       |                   |
| Cross-clamp time                                                        |                    | X                                          |                       |                   |
| Circulatory arrest                                                      |                    | X                                          |                       |                   |
| Fluid in- and output monitoring                                         |                    | X                                          |                       |                   |
| Inotropes and vasopressors                                              |                    | X                                          |                       |                   |
| Laboratory assessments                                           |                    |                                            |                       |                   |
| Chemistry c                                                  |                    | X                                          | X                     |                   |
| Hematology c                                                 |                    | X                                          | X                     |                   |
| Coagulation profile c d                                      |                    | X d                             | X                     |                   |
| Safety labs c                                                |                    | X                                          | X                     |                   |
| Transfusion requirements                                         |                    |                                            |                       |                   |
| RBCs                                                                    |                    | X                                          | X                     |                   |

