| Pooled and apheresis platelets                                          |                    | X                                          | X                     |                   |
| Plasma                                                                  |                    | X                                          | X                     |                   |
| Fibrinogen concentrates                                                 |                    | X                                          | X                     |                   |
| Cryoprecipitate                                                         |                    | X                                          | X                     |                   |
| Other hemostatic products                                               |                    | X                                          | X                     |                   |
| Blood loss determination (e-CABG, UDPB and modified UDPB e ) |                    | X                                          | X                     |                   |
| Extubation time                                                         |                    | X                                          | (X)                   | (X)               |
| ICU length of stay                                                      |                    | X                                          | (X)                   | (X)               |
| Hospital length of stay                                                 |                    |                                            | X                     | (X)               |
| AEs and SAEs                                                            |                    | X                                          | X                     | X                 |
| Concomitant medications                                                 |                    | X                                          | X                     | X                 |

AE, adverse event; CPB, cardiopulmonary bypass; DC, discharge; ICU, intensive care unit; POD, postoperative day; SAE, serious adverse event; UDPB, universal definition of perioperative bleeding; e-CABG, European Coronary Artery Bypass Grafting SDM- Surrogate Decision Maker

\*For any activities not completed during this visit, additional visits will be undertaken to complete activities

a After the start of surgery.

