#### **7.2.2 Transfusion Data**

Details of all blood products and hemostatic agents released from the blood bank and transfused will be collected from the blood bank databases. These include allogeneic blood products (RBCs, pooled or apheresis platelets, and plasma) and albumin. Other hemostatic agents include: desmopressin, fibrinogen concentrates, rFVIIa, idarucizumab, and andexanet alpha.

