### 6.2 Transformations to be applied

In order that the sum of Allogenic Blood Products and its constituents adequately represent the exposure to donors the following transformations will be applied before any derivations:

Platelets:

1 apheresis unit = 4 allogeneic units,  
1 non-apheresis unit = 4 allogeneic units

Frozen Plasma (used in transfusions):

1 apheresis unit = 2 allogeneic units,  
1 non-apheresis unit = 1 allogeneic unit

Transfusion units without any information about apheresis are handled as apheresis units.

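### SAP 6.1 leaves cryoprecipitate out of the allogeneic blood product sums, so cumulative P2 and S3 understate donor exposure whenever it is given

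*Combined protocol and SAP*

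**What the plan says.** SAP 6.1 gives two closed lists. ABP is "Sum of all Allogenic Blood Products (RBCs, FPs and Platelets) transfused in specified time frame". ABPadj is "Adjusted Sum of Allogenic Blood Products (RBCs and Platelets) transfused in specified time frame, I.e. ABP excluding FPs". SAP 4.6 uses these sums for P2 (24 hours) and S3 (to postoperative day 7), with a negative-binomial comparison of the arms. SAP 6.2 states the purpose of the unit conversions, "In order that the sum of Allogenic Blood Products and its constituents adequately represent the exposure to donors", and then gives conversions for platelets and frozen plasma only.

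P3 in SAP 4.6 is "Number of patients who do not receive any allogeneic blood product (in total and for each type separately". S4 is the same count to day 7. SAP 6.1 contains no derivation for either.

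On the protocol side, Table 1 gives "Cryoprecipitate" its own row under "Transfusion requirements" at Visits 1 and 2. Table 4 (section 7.2.3) has a cryoprecipitate column in the UDPB classification. Section 7.2.2 sets a wide scope, "Details of all blood products and hemostatic agents released from the blood bank and transfused will be collected from the blood bank databases", and continues: "These include allogeneic blood products (RBCs, pooled or apheresis platelets, and plasma) and albumin". Cryoprecipitate is named neither there nor among the hemostatic agents that the section goes on to list. Section 1.1, in its account of how PCC is made, describes cryoprecipitate as a fraction of pooled human plasma.

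**The concern.** A sum built to stand for donor exposure should either include every donor-derived component that the trial records as a transfusion or say why one is left out. Cryoprecipitate is recorded and graded, but it has no place in either sum and no conversion. An analyst following the SAP literally gives it zero weight.

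Two results are exposed. The first is the cumulative amount in P2 and S3, with and without FP. The second, depending on how it is programmed, is the total count of patients free of allogeneic products in P3 and S4. P2 and P3 are candidates for the Phase 3 primary endpoint, and protocol 1.2 says the pilot results will feed the Phase 3 sample size, so a gap in the product list would be carried forward.

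**Working it through.** No stated figure depends on the ABP formula. SAP 1.3 says no sample size estimation was made, so there is nothing to reproduce. The check is a trace of definitions followed by illustrative arithmetic.

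**1. Trace of cryoprecipitate**

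- Collected: yes (Table 1, Visits 1 and 2, which cover the 24-hour and day-7 windows).
- Used for UDPB class: yes (Table 4), so it contributes to S2.
- Named in the product list of protocol 7.2.2: no.
- In ABP or ABPadj (SAP 6.1): no.
- Given a conversion (SAP 6.2): no.

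**2. One patient, P2 or S3**

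ABP = RBC + FP + platelets, with SAP 6.2 weights. Take a PCC-arm patient given 2 RBC units, 1 platelet unit (4 allogeneic units) and no FP: ABP = ABPadj = 2 + 4 = 6. Now add c donor units of cryoprecipitate. The documents give no value for c, so 1, 5 and 10 are assumed.

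- c = 1: 6 becomes 7; share missed 1/7 = 14%.
- c = 5: 6 becomes 11; share missed 5/11 = 45%.
- c = 10: 6 becomes 16; share missed 10/16 = 62.5%.

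**3. Arm mean, P2 or S3**

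Let q be the proportion given cryoprecipitate and m the arm mean ABP as now defined. Both are assumed. Shortfall = q × c units per patient; share missed = qc / (m + qc).

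- Low (q = 1%, c = 1, m = 20): 0.01 units; 0.01/20.01 = 0.05%.
- Middle (q = 5%, c = 5, m = 10): 0.25 units; 0.25/10.25 = 2.4%.
- High (q = 15%, c = 10, m = 5): 1.5 units; 1.5/6.5 = 23.1%.
- No use (q = 0): 0.

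The error in the difference between arm means is c × (q in the PCC arm − q in the FP arm). It is zero if use is equal.

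**4. Total count, P3 or S4**

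SAP 3.4 requires every ITT patient to have received PCC or FP. A patient given FP in the window already has an allogeneic product counted, so cryoprecipitate cannot change that patient's status. Misclassification needs a patient treated with PCC who has no RBCs, no platelets, no FP and some cryoprecipitate. With 50 evaluable patients per arm (SAP 1.3), each such patient moves the PCC proportion up by 1/50 = 2 percentage points, two by 4 and five by 10. The shift is in one direction only.

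**5. What is not touched**

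P1, the RBC-free count in P3 and the counts for each listed product type do not depend on the ABP formula.

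**The case against.** The strongest reply is that the SAP follows the protocol. Section 7.2.2 lists RBCs, platelets and plasma as the allogeneic products, and SAP 6.1 uses the same three. A reader who sees only Table 1 beside SAP 6.1 might infer that the SAP departs from the protocol; it does not. What remains is that 7.2.2 is worded as an open list, places cryoprecipitate in no category although Table 1 collects it, and gives no reason for leaving it out. It does not show a deliberate exclusion, and it does not answer the purpose stated in SAP 6.2.

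Second, no sentence in the documents calls cryoprecipitate an allogeneic blood product. Table 1 also lists fibrinogen concentrates and other hemostatic products under the same heading, Table 4 also has PCC and rFVIIa columns, and PCC too comes from pooled plasma but is not in the sum. This stands: the classification is an inference from several places together, and the documents should settle it.

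Third, SAP 4.6 treats P3 as a categorical endpoint and nowhere says that it is computed as ABP = 0. This stands too, so the P3 and S4 part is conditional.

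Fourth, cryoprecipitate does not vanish from the report. S2 covers the individual UDPB components, and SAP section 4 has all recorded data listed. That preserves visibility but does not repair the sums.

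**Conclusion.** The omission is real. As written, ABP and ABPadj give cryoprecipitate no weight, so cumulative P2 and S3 fall short of donor exposure by its donor units whenever it is given. If P3 and S4 use the same three-class list, a cryoprecipitate-only patient is counted as free of allogeneic products, in practice only in the PCC arm, at 2 points per patient with 50 per arm.

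The documents cannot fix the size. Over the assumed ranges above, the P2 shortfall runs from 0.05% to 23% of the arm mean; if the sites give none, nothing changes.

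Two stronger readings are tempting but not supported. One is that the P2 treatment comparison is biased. Protocol 1.1 says PCC lacks the full balance of factors found in FP, but nothing there says that fibrinogen replacement, or cryoprecipitate use, would differ by arm. The other is that S6 is wrong because it counts fibrinogen concentrate alone. S6 reproduces the protocol's own exploratory endpoint, and adding cryoprecipitate would create a new endpoint.

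**What to change.** - SAP 6.1: add cryoprecipitate to ABP and ABPadj.
- SAP 6.2: state its donor-unit conversion, based on the product as supplied to the sites.
- SAP 6.1: write a derivation for P3 and S4 that names the products in the total, including cryoprecipitate.
- Protocol 7.2.2: bring the product list into line with Table 1 and the revised SAP.
- Report the three-class sum as a sensitivity analysis, so that the effect of the added product and of its conversion factor can be seen.

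The cost is a few lines of SAP and protocol text and one more variable in the derivation, from data that Table 1 already schedules. The small downside is that a conversion factor must be chosen; the sensitivity analysis makes that choice visible. The change should be made before any unblinded analysis, which is when SAP 2.1 requires the plan to be final.
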